#### Circulatory State Transitions During Post Cardiac Arrest Syndrome

During critical illness, most patients go through different states of hemodynamic stability. We have categorized the circulatory state after CA in 3 different categories based on data obtained from routine care (Table 1). Every 10 min, a patient is classified according to the least favorable measurement at that time (eg, isolated MAP of 40 mm Hg is sufficient to classify a patient to have severely disturbed circulation).

We will validate the appropriateness of the defined categories against the cardiac index.

Patients may go back and forth between the clinical states, defined in Table 1, corresponding to the severity of their illness and its progression (Figure 2), and the changes from one clinical state to another will be recorded. By using survival analysis methodology, we allow for right censoring, which means that the information from patients with limited follow-up time can be included in the analyses. A patient who is in a certain clinical state at time *t* might remain in the same state or change to one of 2 others at time *t* +1. In such multi-endpoint settings, the clinical states compete with each other, and the transitions over time are best studied with methods developed for competing risk analyses.

**Table 1 table1:** Circulatory states.

Variables	Circulation		
	Undisturbed	Disturbed	Severely disturbed
Mean arterial pressure, mm Hg	≥65	45-64	<45
Heart rate, bpm	51-100	<50, 101-130	≤40, >130
Lactate, mmol/L	<2	2–4	>4
ScvO_2_, %	≥65	50-64	<50
Fluid resuscitation, L/hours	<0.5	0.5-1.9	≥2
Norepinephrine, μg·kg^−1^·min^−1^	<0.1	0.1-0.29	≥0.3
Dobutamine, μg·kg^−1^·min^−1^	No	<10	≥10
Vasopressin	No	No	Yes
Epinephrine	No	No	Yes
Levosimedan	No	No	Yes
Aorta balloon pump	No	No	Yes

**Figure 2 figure2:**
[figure not shown]
Possible transitions between circulatory states.

The Kaplan-Meier estimator accurately estimates the transition from one state to another, assuming that these 2 states describe all possible states. To be useful in a competing risk framework, the Kaplan-Meier estimator has been generalized into a matrix version, called the Aalen-Johansen estimator. To describe when, in time, most state transitions occur (ie, transition intensity), we will use the Nelson-Aalen estimator. The Nelson-Aalen estimator is a nonparametric estimator of the “cumulative hazard” of a given event, and it can be applied in a multi-state model.

#### Patterns Predictive of Deterioration in Circulatory State

We anticipate that not all patients will follow the same circulatory trajectory; during the study, some will deteriorate and some will improve in circulatory status, and during our observation, many will have several state transitions. We plan to analyze events before deteriorations to identify patterns of circulatory and inflammatory response measurements predictive of clinical state deteriorations. These patterns will be compared with those in patients who improve their circulatory status or remain unchanged.

To explore the predictive value of previous measurements to foresee a clinical deterioration, we will use 2 different approaches. The outcome variable will be dichotomized to deterioration versus no deterioration (status quo or improvement). First, we will test different timelags between measurements and deteriorations to see which is more informative (eg, 1 hour, 2 hours, 3 hours). For this analytic approach, we will use univariable and multivariable logistic regression. Second, we will use methods from survival analysis to assess continuous alterations in covariates on the outcome. For this analysis, we will use Aalen’s linear model, which is an intensity regression model. Variables from the 2 groups will also be explored in respect to its relation to mortality and CPC at discharge from hospital.

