### Censoring

Patients are censored from further follow-up if the patient undergoes acute cardiothoracic surgery or intervention with extracorporeal membranous oxygenation support or a ventricular assist device, at the time of death, if life-prolonging therapy is withdrawn or withheld, or when the patient is transferred to a general ward or another hospital. The reason for censoring is recorded, and all data obtained until censoring will be included in the analysis.

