Standard critical illness classification systems, such as SAPS II, SAPS III, acute physiology and chronic health evaluation (APACHE) II, SOFA, or New Early Warning (NEW) scores, are not applicable to describe circulatory changes during the acute phase of PCAS. SAPS and APACHE scores are developed to define risk at admission. SOFA and NEWS scores will reach a ceiling effect and not be able to differentiate between various degrees of circulatory failure in this population. Some researchers have used an extended SOFA circulatory score where 4 further increments are added to the standard circulatory SOFA score [39]. However, this score only includes arterial blood pressure and use of vasopressors, which may not encompass all relevant observations for circulatory stability. Therefore, this study classifies the patients into 3 circulatory groups: *undisturbed, disturbed*, or *severely disturbed circulation* based upon predefined values of mean blood pressure, heart rate, serum lactate concentration, ScvO_2_, use of fluid, vasoactive drugs, and the need for mechanical circulatory devices. Cut-off values were based upon relevant guidelines and clinical practice. All variables were selected because of their known relevance to circulatory failure and because they are easily available during routine monitoring of critically ill patients. More precise measures such as CO or SvO_2_ were not included, as these are usually not obtained in patients after CA.

The clinical trajectories in the acute phase of PCAS are heterogeneous, as seen from the lack of circulatory stability. Such changes can occur immediately after admittance to the ICU or later, at any time, in the clinical course. Thus, the patients are at constant risk. Limited information exists regarding the factors to identify which patients are at the highest risk of imminent clinical circulatory failure. Such factors may include characteristics of the CA episode or clinical observations in the ICU.

This study will establish which factors—demographic, CA-related variables, or clinical observations— will predict circulatory failure and, thus, assess circulatory stability during PCAS.

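### Time that starts in the severely disturbed state cannot count as deterioration, yet the logistic models score it as no deterioration, which biases odds ratios for severity-linked predictors downward

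*Protocol article*

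**What the plan says.** All references are to the protocol article.

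- **Scale** (Circulatory State Transitions During Post Cardiac Arrest Syndrome): "We have categorized the circulatory state after CA in 3 different categories based on data obtained from routine care (Table 1"). Severely disturbed is the worst category. "Every 10 min, a patient is classified according to the least favorable measurement at that time".
- **Possible moves** (same section): a patient "might remain in the same state or change to one of 2 others at time" the next time point. From the worst state, both moves are improvements.
- **Censoring** (Censoring): follow-up stops "at the time of death, if life-prolonging therapy is withdrawn or withheld", and also at acute cardiothoracic surgery, ECMO or a ventricular assist device, and at transfer.
- **Outcome** (Patterns Predictive of Deterioration in Circulatory State): "The outcome variable will be dichotomized to deterioration versus no deterioration (status quo or improvement").
- **Comparison group** (same section): "These patterns will be compared with those in patients who improve their circulatory status or remain unchanged".
- **Models** (same section): univariable and multivariable logistic regression at several time lags, then Aalen's linear intensity model. Neither description mentions the starting state or which intervals are eligible.

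**The concern.** A patient who is already severely disturbed can only stay, improve or be censored. The stated coding puts staying and improving in the same non-event group as a stable, undisturbed patient. The sickest observed time thus enters the logistic comparison as time without deterioration, although deterioration was impossible there.

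The candidate predictors are haemodynamic, inflammatory and endothelial measurements, studied because they may track circulatory failure. Such markers are likely to be most abnormal in severe time, so loading that time onto the non-event side weakens their apparent association with deterioration. A marker that only delays recovery could even look protective.

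This bears on the fourth research question, which clinical characteristics and biomarkers predict changes of state, and on the prediction model announced in the Discussion. The Discussion sets SOFA and NEWS aside because they "will reach a ceiling effect and not be able to differentiate between various degrees of circulatory failure in this population"; the deterioration outcome has a ceiling of its own, at the severely disturbed state.

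**Working it through.** The protocol gives no effect size, event count or state frequency (Sample Size calls the frequencies largely unknown), so there is no figure to reproduce. All rates below are assumptions. Each 10-minute interval is scored relative to the state in which it starts.

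**1. Closed form, binary marker.** Let p0 and p1 be the probabilities of deterioration in at-risk intervals with a low and a high marker, and sL and sH the shares of low- and high-marker intervals that start severe. Severe intervals score 0, so

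OR(all) = odds[p1(1 − sH)] / odds[p0(1 − sL)], and OR(all) = 1 when sH = 1 − p0(1 − sL)/p1.

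Take p0 = 0.05 and a true OR of 2.0. Odds of p0 are 0.05/0.95 = 0.0526, doubled 0.1053, so p1 = 0.1053/1.1053 = 0.0952.

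Example, sL = 10%, sH = 30%: low 0.05 × 0.9 = 0.0450, odds 0.0471; high 0.0952 × 0.7 = 0.0667, odds 0.0714; ratio 1.52.

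| Severe share, low / high marker | OR(all), true 2.0 |
|---|---|
| 10% / 10% | 1.99 |
| 30% / 30% | 1.97 |
| 10% / 20% | 1.75 |
| 10% / 30% | 1.52 |
| 10% / 40% | 1.29 |
| 10% / 50% | 1.06 |
| 10% / 60% | 0.84 |

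Break-even with sL = 10%: 1 − 0.045/0.0952 = 53%. Over p0 from 0.02 to 0.20 it is 46% to 54%. For a true OR of 1.5 it is 34% to 39%; for 3.0, 58% to 69%.

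**2. Continuous marker, simulated logistic regression.** 400,000 intervals, at-risk intercept −2.5, marker mean shifted upward in severe intervals. Odds ratios per SD from all intervals:

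| True OR | Severe share | Shift 0 | 0.5 SD | 1.0 SD | 1.5 SD |
|---|---|---|---|---|---|
| 2.0 | 10% | 1.97 | 1.82 | 1.65 | 1.50 |
| 2.0 | 25% | 1.93 | 1.65 | 1.39 | 1.19 |
| 2.0 | 40% | 1.95 | 1.52 | 1.18 | 1.01 |
| 1.5 | 25% | 1.47 | 1.28 | 1.11 | 1.00 |
| 1.5 | 40% | 1.49 | 1.17 | 0.96 | 0.85 |

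At-risk intervals alone give 1.97 to 2.03 and 1.48 to 1.52.

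**3. Three-state simulation in 10-minute steps, marker fixed per patient.** Five days are 5 × 24 × 6 = 720 steps.

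| Assumed marker effect | Severe share | OR, all intervals |
|---|---|---|
| Deterioration 2.0, improvement 0.5 | 38% | 1.01 |
| Deterioration 2.0, no effect on improvement | 37% | 1.36 |
| Deterioration 2.0, no effect on improvement | 14% | 1.52 |
| None on deterioration, slows recovery only | not tabulated | 0.75 to 0.82 |

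For a true OR of 2.0, restricting to at-risk intervals gives 1.61 to 1.89; adding a starting-state term gives 1.96 to 2.01. Here the marker also separates undisturbed from disturbed time, so restriction alone does not suffice.

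**The case against.** The strongest reply is that the quoted sentence defines how the outcome is coded, not which intervals enter the model, and that an article may leave the risk set to a fuller document. The multi-state estimators in the preceding section do condition on the current state. This stands in part: a fuller plan could exclude severe time. But the article goes beyond silence. It names the comparison group as those who improve or remain unchanged, and that description covers everyone in severe time who is not censored. The multi-state estimators describe transitions; they are not the logistic model.

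Four stronger readings are tempting, and the protocol does not support them.

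- **That predictors are certain to vanish or change sign.** This depends on the severe share and on how strongly the marker tracks severity; the protocol gives neither. The near-null result at 38% severe time also needs a marker fixed for five days and a reciprocal effect on improvement. With a time-varying marker (10-minute autocorrelation 0.99) a true 2.0 gives 1.34, and at autocorrelation 0.96 it gives 1.67. Biomarkers are sampled daily and the plan studies changing covariates, so these milder cases matter.
- **That both models are equally affected.** Aalen's model carries an at-risk indicator and can already exclude severe time. The text does not say that it will.
- **That the whole gap is due to the ceiling.** Part of it is confounding by starting state, as the results for restriction alone show.
- **That this is the main analysis.** The protocol names no primary analysis and calls this work exploratory.

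**Conclusion.** The point holds for the logistic models. Followed as written, the coding counts intervals that can never be events as non-events, and this biases odds ratios for severity-linked predictors of deterioration downward. Under the assumed rates, a true odds ratio of 2.0 becomes roughly 1.0 to 1.6 with 14% to 38% severe time. The bias is negligible (1.93 to 1.99) when the marker is unrelated to severe status; under a strong link the odds ratio may be nullified or reversed. With 50 patients, attenuation alone could hide real predictors.

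The direction follows from the protocol's text, provided that the marker is more abnormal in severe time. The size does not: it rests on assumed transition rates, severe shares and marker behaviour. For Aalen's model the point is only that the at-risk definition should be stated.

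**What to change.** 1. Restrict the logistic deterioration models to intervals that start undisturbed or disturbed.
2. In addition, stratify by or adjust for the starting state. Both steps are needed.
3. State that the at-risk indicator for deterioration in Aalen's model is zero during severely disturbed time.
4. Report the share of intervals that start severely disturbed.
5. Analyse those intervals separately: improvement versus remaining, with death, ECMO and ventricular assist device as competing events.

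The cost is analysis-plan wording. No new data are needed, since the reason for censoring is already recorded. The downside is that severe intervals leave the deterioration model and are reported in their own.

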### Sample Size

This is an observational study, and the frequency of abnormal biomarkers, circulatory states, and endpoints are largely unknown; therefore, no formal sample size calculation has been performed [24]. On the basis of a sample size from similar studies describing pathophysiology, we aim at including 50 patients [21,25].

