#### Biomarkers

As part of the study, we will establish a biobank for analysis of inflammatory and endothelial biomarkers. Blood samples will be taken at inclusion and every morning the 5 following days. After gentle mixing, the blood samples are placed vertical for 30 min in ambient temperature, and then centrifuged at 2200 g for 10 min. The supernatants are stored at −80°C within 1 hour from the time of sampling. During the study period, additional full blood will be drawn and stored at −80°C.

We will analyze the following biomarkers: interleukin (IL)-1β, IL-1 receptor antagonist (IL1-ra), IL-2, IL-4, IL-5, IL-6, IL-7, IL-8, IL-9, IL-10, IL-12 (p70), IL-13, IL-15, IL-17, eotaxin, basic fibroblast growth factor, granulocyte-colony stimulating factor, granulocyte macrophage colony stimulating factor, interferon γ, interferon-inducible protein 10, monocyte chemotactic protein 1, macrophage inflammatory protein 1α and 1β, platelet derived growth factor-BB, regulated upon activation T cell expressed and secreted, tumor necrosis factor, vascular endothelial growth factor, syndecan-1, sE-selectin, heparan sulfate, hyaluronic acid, soluble trombomodulin, and sVE-cadherin. Other biomarkers of interest, identified later, may be included in the final analysis.

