## Discussion

### Rationale for This Study

This study will describe the hemodynamic and inflammatory response characteristics of circulatory failure in PCAS. On the basis of the findings, we will develop a prediction model for risk of circulatory failure in PCAS.

PACS after CA is frequent, and it is strongly associated with mortality after CA [4]. However, there is relatively limited information about the detailed circulatory disturbances in PACS, and principles for circulatory supports are partly transferred from other conditions, in particular, in the treatment of septic shock. Moreover, the expected course (eg, improvement or deterioration) of the circulation is not well understood. The clinical trajectory may be 2-phased: first, a low CO state, followed by a low peripheral resistance state, as previously proposed [20]. Alternatively, it may be one-phased: predominantly caused by either an isolated cardiac failure or an isolated vasoplegia. It is also not established which patients are at a higher risk for circulatory failure in the acute phase of PCAS.

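### Choosing the time lag and predictors on the same 50 patients, from 33 or more biomarkers plus clinical variables, makes a resulting prediction model likely to look better than it is

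*Protocol article*

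**What the plan says.** The section Patterns Predictive of Deterioration in Circulatory State reduces the outcome to deterioration versus no deterioration. For the first of two approaches it says "we will test different timelags between measurements and deteriorations to see which is more informative (eg, 1 hour, 2 hours, 3 hours", and continues: "For this analytic approach, we will use univariable and multivariable logistic regression". The second approach is Aalen's linear model.

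The Biomarkers section lists the candidates by name and leaves the list open: "Other biomarkers of interest, identified later, may be included in the final analysis". The Research Questions ask which clinical characteristics and which biomarkers predict a change of state, so both kinds of variable are candidates.

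Under Sample Size, "we aim at including 50 patients" and "no formal sample size calculation has been performed". The number is taken from earlier studies that described pathophysiology.

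The Discussion (Rationale for This Study) says that on the basis of the findings "we will develop a prediction model for risk of circulatory failure in PCAS". Later in the same section comes "This study will establish which factors", followed by demographic, arrest-related and clinical factors, as predictors of circulatory failure. The methods text sets the weaker aim of exploring predictive value.

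**The concern.** Three choices are made on the same data that estimate the effects: which lag to use, which variables to carry forward, and which biomarkers to add to an open list. Each choice favours whatever happened to separate the patients well in this sample. A model built from the winners then shows discrimination that partly reflects the choosing.

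This does not depend on within-patient correlation. It arises even with one row per patient. Repeated deteriorations add rows, but the rows belong to the same 50 people.

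At stake is the use of the result. If the model is reported with its apparent accuracy, or the factors as established, readers may take chance findings into later studies or bedside risk assessment. Under Expected Limitations the article itself restricts long-term outcomes to description because the cohort is small. It applies no such caution to the prediction model for circulatory failure.

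**Working it through.** The article gives no calculation for this analysis, so there is no figure of its own to reproduce. The check asks what selection alone would produce if no marker carried information.

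**Inputs from the article**
- Patients: 50 (Sample Size).
- Named biomarkers: 27 from IL-1β to vascular endothelial growth factor, plus 6 from syndecan-1 to sVE-cadherin, giving 33 (Biomarkers).
- Event rate: the only one given is 73/165 = 44% in an earlier cohort (Inflammation and Circulatory Failure). Applied here, 50 × 73/165 = 22.1, or about 22 patients.
- Biomarker sampling: at inclusion and each morning (Biomarkers).

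**Assumptions**
- Two-sided 0.05, one row per patient, one lag, all 33 markers null.
- Markers either independent or pairwise correlated at 0.5.
- For the AUC illustration, the four best markers go into one model.

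**Step 1: information per candidate.** 22/33 = 0.67 patients with the event per named biomarker. At event rates of 30% or 70% the smaller outcome group has 15 patients, and 15/33 = 0.45. Clinical candidates and later biomarkers lower this further.

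**Step 2: false positives.** Expected number = 33 × 0.05 = 1.65, whatever the correlation. Chance of at least one, if independent = 1 − 0.95^33 = 81.6%. Simulation with rank-based tests gives 79 to 81% for independent markers and 54 to 55% at correlation 0.5. Wald tests from the logistic model are somewhat conservative at this sample size: 74% and 45%, with about 1.3 to 1.4 false positives on average.

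**Step 3: apparent accuracy when the true AUC is 0.50** (simulated)

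| Model | Independent | Correlation 0.5 |
|---|---|---|
| Best four markers | 0.79 (5–95% range 0.72–0.86) | 0.73 |
| Markers kept at p<0.05, where any | 0.75 | 0.72 |
| All 33 markers | 0.99 | 0.97 |

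The best single independent marker has an apparent AUC of 0.69 (0.64–0.76).

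**Step 4: what lag choice adds.** With one sample a day, a 1-hour and a 3-hour lag point to different samples only when a draw falls in the two hours between them. They share the sample for about 22/24 = 92% of event times, so lag choice adds little for biomarkers. It matters more for variables recorded each minute or hour. There, taking the best of three lags raises the error rate per variable from 5% to 7.7% if adjacent lags correlate at 0.95, to 10% at 0.8, and to 13% at 0.5.

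**The case against.** The strongest reply is that the analysis text is openly exploratory, and that penalisation, internal validation and multiplicity control belong in an analysis plan that is not shown. Their absence from a condensed article is indeed no finding. The point rests on what the article does state: a lag chosen on the data, an open candidate list, 50 patients, and a prediction model to follow.

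Several stronger readings are tempting but not supported:

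- **That the article claims to establish which biomarkers predict failure.** The sentence containing "This study will establish which factors" goes on to demographic, arrest-related and clinical factors and does not list biomarkers. The biomarker link comes from the Research Questions and the section on predictive patterns. The mismatch between *establish* and *explore* is real, but it concerns those other factors.
- **That the article prescribes a significance screen followed by a best-four model.** It names logistic regression and no selection rule, and it promises no AUC. The figures above illustrate an assumed procedure.
- **That three lags turn 33 tests into 99.** Daily sampling makes the lags largely the same test for each biomarker.
- **That the selected predictors will be mostly chance.** This would require nearly every marker to be uninformative, which is unknown. Even with every marker null and correlation 0.5, roughly 45% of studies would show no false positive.

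The 22 events are also borrowed from a normothermic cohort. Here the state is classified every 10 minutes and patients may deteriorate repeatedly, so the one-row simulation is simpler than the planned analysis. None of this removes the optimism that comes from selecting and assessing on the same patients.

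**Conclusion.** The concern holds in a limited form. Choosing lag and predictors on the 50 patients who also fit the model is likely to give some false predictors and an over-optimistic apparent accuracy. Under the stated null assumptions, about 1.65 false positives are expected from the named biomarkers at one lag, with a chance of about 55% to 80% of at least one. A four-marker model shows an AUC of about 0.73 to 0.79 for no real discrimination. The level of 0.05, the event rate, the correlation and the selection procedure are assumptions. The direction of the bias in apparent accuracy was the same in every null scenario run.

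Separately, the Discussion's claim to establish demographic, arrest-related or clinical predictors is stronger than the exploratory analysis can support. This should be corrected before results are reported. It does not undermine the descriptive aims of the study.

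**What to change.** - For any prediction model, repeat the whole process of lag choice and predictor selection inside a bootstrap that resamples patients, not observation windows. Report optimism-corrected discrimination and calibration beside the apparent values.
- Preferably use a penalised fit. With fewer than one event per candidate it will not guarantee a useful model, but the corrected figures will show whether there is one.
- Report biomarkers added to the named list later as post hoc, separately from the 33.
- State which lags were tried and show results for all of them.
- In the Discussion, change *will establish* to *will explore*, and extend the small-cohort caution under Expected Limitations to the prediction model.
- Optionally, control the false discovery rate across the univariable results.

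The cost is more analysis work and a less favourable reported accuracy. No new patients or measurements are needed.
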